### Data Curation

The data used in this study will be obtained from different databases, which must be merged for the analysis. None of the databases will be sorted by patient but by other types of entries (drugs, diagnoses, procedures performed, etc); therefore, the same patient could appear multiple times in each of them. Thus, first, a date will be associated with each event, and the information in the databases will be sorted by patient, with each patient as an entry that appears only once.

The coding of diseases and therapeutic procedures has undergone changes during the years of collection in the cohort, transitioning from using International Classification of Diseases, Ninth Revision (ICD-9) coding to ICD-10 coding. Consequently, all the data with ICD-9 coding will have to be converted to ICD-10 using the conversion tables provided by the Government of Catalonia (Generalitat de Catalunya) on their website [15].

In the pharmacological dispensing database, the active principles will be collected through the Anatomical Therapeutic Chemical (ATC) Classification System, and the amount dispensed monthly will be determined using the number of defined daily doses (DDDs) [16]. DDDs change over the years and are not uniform for different active ingredients or for drugs that form different groups as defined by the ATC4 codes. Thus, when necessary, DDDs will be transformed into units of mass for each of the drugs using the tables provided by the WHO with the evolution of DDDs over time [17].

One of the databases managed includes patients with metastases of any origin. For these patients, their previous diagnoses will be traced, and all the codes for both the CMBD and the ECAP will be analyzed to search for cancer diagnoses before metastasis to determine the origin of the cancer.

Finally, a patient rejection process will be applied based on the consistency of dates between the different databases. Following this principle, all those patients who, having been included in the database, do not have electronic prescription records will be rejected. In addition, all patients without registration or enumeration in the death databases will be excluded. Finally, patients with inconsistent dates will be excluded, for example, with postdeath records in the CMBD, ECAP, or electronic prescription.

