### Participants and Settings

The study population will be patients with the following cancers whose estimated survival at 5 years is less than 20%: lung, pancreas, esophagus, gastric carcinomas, hepatocarcinoma, and metastatic cancers.

Cohort 1 will include all patients registered in the databases of the public health system in Catalonia (Spain) who were diagnosed with any of the diseases under study between 2006 and 2012 (Textbox 1 contains the list of International Classification of Diseases, Tenth Revision [ICD-10] codes) and who have complete data regarding the study variables (see “Outcome Measurements and Variables” section).

Diagnostic codes (International Classification of Diseases, Tenth Revision [ICD-10]) for the pathologies under study.

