### Duration

The patients in cohort 1 will have been diagnosed with the cancer under study between 2006 and 2012, both inclusive, and their survival will be retrospectively monitored for 5 years after diagnosis or until death if it occurs earlier. Cohort 2 will include patients without cancer who have had any type of contact with the health care system between 2006 and 2012, and these individuals will be followed up retrospectively for 5 years or until death if it occurs earlier.

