Hospital CMBD is a database in which diagnoses and procedures performed on hospitalized patients are recorded throughout the Spanish territory; all public hospitals and the majority of private hospitals (>95% hospital coverage) are included [14].Estació Clínica d'Atenció Primària (ECAP) is an electronic medical history program launched in 2001 and used by family doctors, pediatricians, and nurses from the Catalan Institute of Health (Institut Català de la Salut [ICS]) primary care centers when they visit patients; it includes all previous illnesses known to the primary care physician and records of the health care process in the outpatient setting, including assessments by health care personnel, diagnostic tests, and treatment, among others. The PADRIS program has only provided data since 2006, after which data are considered to be of good quality.The registry of causes of death is prepared by the INE using data from the Medical Certificate of Death or Statistical Bulletin of Death, Statistical Bulletin of Judicial Death, and Statistical Bulletin of Childbirth. It is prepared following the criteria established by the WHO (World Health Organization) in the International Classification of Diseases (ICD), which includes more than 12,000 diseases.Electronic prescription has been implemented in Catalonia progressively since 2010 and is currently deployed in 100% of primary care centers, pharmacies, and public hospitals in Catalonia. Prescribing and dispensing data will be obtained from the Comprehensive Health Information System of the Catalan Health Service (Servei Català de la Salut [CatSalut]), which is a computerized system used by the doctors of the national health system in Catalonia to prescribe financed pharmacological treatments to their patients and the pharmacies to dispense them; it contains information on the date of the prescription, the active ingredient, and dose, among other variables. Unfunded treatments can be prescribed using this tool but are often prescribed by other means (paper prescriptions).

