### Outcome Variables and Measurements

The primary end point is survival, calculated from the date of entry in the database until death or until 5 years of follow-up are reached. For patients in cohort 1, the earliest date of cancer diagnosis for which they have been selected to be part of the cohort will be considered the date of entry into the study (inclusion criterion).

As study variables, the following data will be collected from all patients:

List of diagnosed diseases (data source: CMBD and ICS ECAP diagnostic registry)Date of death (data source: INE cause of death registry)Cause of death (data source: INE cause of death registry)Pharmacological treatment (data source: Catalan electronic prescription), including all prescribed active ingredients, drug withdrawal dates from pharmacies, consumed doses, and prescribed regimen, during the entire follow-up periodSex (data source: Sistema Integral d'Informació de Salut)Date of birth (data source: Sistema Integral d'Informació de Salut)Basic health area (data source: Sistema Integral d'Informació de Salut)

For the patients included in the study with one of the cancers under study (cohort 1), the following variables will also be collected:

Type of cancer and presence of metastases (data source: CMBD and ICS ECAP diagnostic registry)Date of diagnosis for which the patient is included in the cohort (data source: CMBD and ICS ECAP diagnosis registry)Surgical treatment of the cancer (data source: CMBD)Date of surgical treatment (data source: CMBD)

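### As written, patients diagnosed in 2006–2009 enter the drug analyses only if they survive to the electronic prescription rollout that began in 2010, and diagnosis year is not a named matching or adjustment variable

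*Protocol article*

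**What the plan says.** Participants and Settings defines cohort 1 as patients "who were diagnosed with any of the diseases under study between 2006 and 2012" and also requires that they are people "who have complete data regarding the study variables". Duration confirms the window as "diagnosed with the cancer under study between 2006 and 2012, both inclusive" and adds that "their survival will be retrospectively monitored for 5 years after diagnosis or until death if it occurs earlier".

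Outcome Variables and Measurements fixes time zero: "the earliest date of cancer diagnosis for which they have been selected to be part of the cohort will be considered the date of entry". The same section names the exposure source: "Pharmacological treatment (data source: Catalan electronic prescription". Data Sources dates that source: "Electronic prescription has been implemented in Catalonia progressively since 2010". Data Curation then sets the exclusion: "all those patients who, having been included in the database, do not have electronic prescription records will be rejected".

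Methods to Address Potential Sources of Bias handles immortal time with a landmark after diagnosis, month 3 being the example. Patients who first use the drug after the landmark are dropped, and the comparison group is never-users. Statistical Analysis plans matching on confounders that it does not list. If imbalance remains, it adjusts for age, sex and diagnostic groups.

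**The concern.** Four of the seven diagnosis years precede the earliest date on which an electronic prescription record could exist. Someone diagnosed in 2006 who died before 2010 cannot have a record and is rejected. Someone diagnosed in 2006 who reached 2010 is kept, with three to four years of guaranteed survival counted in the endpoint. Inclusion therefore depends on the outcome (left truncation without delayed entry).

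The same patients have almost no recorded exposure in the early window that the landmark uses. An early user with no later record is read as a never-user. An early user whose records begin after rollout looks like a late starter and is deleted. Diagnosis year then drives both measured exposure and apparent survival, so it confounds every drug screened.

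The sensitivity analysis that uses deaths in year 1, 2 or 3 is affected too. Patients diagnosed in 2006 can supply no deaths in years 1–3, those diagnosed in 2007 none in years 1–2, and those diagnosed in 2008 none in year 1.

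**Working it through.** The article gives no figure for this selection. Its sample size of 294 per group (20% versus 30%, two-sided 5%, 80% power) reproduces with the pooled normal approximation but does not bear on the point.

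**Inputs from the article.** Diagnosis years 2006–2012; electronic prescription from 2010 at the earliest; 5-year survival S5 of 18.1% for lung and 8.2% for pancreas (Table 2), with an overall ceiling of 20%.

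**Assumptions.** Constant hazard, even accrual, and full coverage on 1 January 2010. The last is lenient, because the rollout was progressive.

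**Step 1: selection by diagnosis year.** The hazard is λ = −ln(S5)/5, which is 0.342 per year for lung and 0.500 for pancreas. The share kept is the mean over the year of exp(−λ·(2010 − t)), where t is the diagnosis date. Every 5-year survivor diagnosed from 2006 on reaches 2010, so apparent survival is S5 divided by the share kept. For lung in 2006 this is 0.181/0.304 = 0.60.

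| Diagnosis year | Lung: kept | Lung: apparent S5 | Pancreas: apparent S5 |
|---|---|---|---|
| 2006 | 30% | 60% | 47% |
| 2007 | 43% | 42% | 28% |
| 2008 | 60% | 30% | 17% |
| 2009 | 85% | 21% | 10% |
| 2010–2012 | 100% | 18.1% | 8.2% |

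For lung, 54% of all 2006–2009 diagnoses are kept, with apparent survival 0.181/0.545 = 33%.

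**Step 2: effect on a drug comparison.** This is a simulation. The drug has no effect, 20% of patients use it in the first three months, and nobody starts later. S5 is 20%, the landmark is month 3, and use is visible only if the three-month window reaches the coverage date.

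- Coverage on 1 January 2010: 5-year survival is 21.7% in recorded users and 28.8% in recorded non-users. The crude odds ratio is (0.217/0.783)/(0.288/0.712) = 0.69.
- Coverage dates spread evenly over 2010–2012: 21.7% versus 33.5%, crude odds ratio 0.55. It is 0.57 if the record must fall within the five years of follow-up.

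**Step 3: would diagnosis year repair it?** Stratifying the same simulation by calendar year of diagnosis gives a pooled odds ratio of about 0.99 with immediate coverage and about 0.96 with the spread rollout. The 2006–2008 strata hold no recorded users and contribute nothing. The remaining bias sits in the years that straddle coverage: about 0.90 in 2009 with immediate coverage, and about 0.84 in 2010 with the spread rollout.

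**The case against.** The strongest reply is that usable drug data may begin before 2010. Data Sources says that prescribing and dispensing data come from the CatSalut information system, Data Curation speaks of a dispensing database, and Outcome Variables and Measurements promises treatment data for the whole of follow-up. If dispensing records reach back to 2006 and electronic prescription is loose shorthand, the main bias largely disappears. This stands as a possibility. A reader might infer that drug data before 2010 certainly do not exist, and the article does not say so. Nor does it say that they exist: its statement about data from 2006 is in the primary care record entry, which is not the named drug source. Both the exposure definition and the rejection rule name electronic prescription, so the text needs changing either way.

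A reader might also infer that no planned method can repair the bias. Step 3 shows otherwise: the planned matching would remove most of it if it included diagnosis year. The gap is that year is not named. The landmark alone does not help, although month 3 is only an example.

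The survival figures in Step 1 are absolute levels, whereas the objective is a contrast between drug groups. That is fair, and Step 2 is the relevant measure. It is one illustration, and it does not show that every drug will look harmful by this amount.

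The plan discards findings that recur in the control cohort. This could screen out an artefact common to both cohorts, but it cannot recover an association that the bias has masked. The exploratory label and the deferral of substudy details to later papers answer chance findings and missing detail. They do not answer a stated inclusion rule that conflicts with the article's own dates.

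**Conclusion.** The point holds on the text as written, and it should be settled before drug results are reported; Results says that analyses have begun. The rejection rule, the 2010 start of the named drug source and the 2006–2012 window cannot stand together with survival counted from diagnosis.

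That survival is inflated in the pre-2010 diagnoses follows from the rule itself. The sizes rest on the constant hazard, even accrual and assumed coverage dates. The crude odds ratios of 0.69 and 0.55 rest further on the assumed 20% use, 20% survival and no later starters. All of it is conditional on there being no usable dispensing data before the rollout, which the article leaves open.

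**What to change.** 1. State the first date of usable dispensing data and reconcile Data Sources, Outcome Variables and Measurements and Data Curation with the 2006–2012 window. If CatSalut dispensing data cover 2006 onward, say so and base the rejection rule on them.
2. Otherwise, restrict the primary drug analyses to patients diagnosed on or after the date dispensing data cover their basic health area. Use earlier diagnoses only in a sensitivity analysis with delayed entry at that date.
3. Within covered areas and dates, keep patients with no dispensing as unexposed. The current rule removes genuine non-users from the comparison group.
4. Name diagnosis year among the matching and adjustment variables.
5. Apply the same rule to the control cohort.

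**Cost.** Mostly wording and a filter. Basic health area is already collected, but its coverage date is not among the listed variables. That date would have to come from CatSalut or be read from the first records seen in each area. The cohort shrinks: if the 102,860 patients are spread evenly over the seven years and coverage is full from 2010, at most about 102,860 × 3/7 ≈ 44,000 remain, and fewer with a phased rollout. Nearly all of those dropped have no exposure recorded in the early window.

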### Statistical Analysis

To achieve the primary objective, several exploratory analyses will be performed. These will look for an association between the use of the different drugs available in the database (the exposure variable) and patient survival (the outcome variable). The exposure variable will be treated both dichotomously (exposed or not exposed) and quantitatively. The time exposed to the drug, the average monthly dose, the maximum dose, or the cumulative dose per unit of time will be considered. Specific analyses will be carried out on the effect of 2 or more drugs that have been shown to influence survival when they have been consumed, either simultaneously or sequentially, within the time unit being analyzed. The outcome variable is survival during the observation period. Patients who are censored, for whom no death is recorded during the follow-up time, are considered alive at the end of the period.

In addition to the machine-learning techniques described above, the association between exposure and outcome will be investigated using 2 different approaches. The exposure odds for each drug will be calculated, and this exposure will be compared between patients considered alive at 5 years and those who have died using odds ratios (exposure odds ratio). The group of nonsurvivors will be selected with different time criteria in a sensitivity analysis: deceased in the 1st, 2nd, or 3rd year after diagnosis. Second, the survival time of participants exposed and unexposed to each drug available in the database (individual agents, ATC5 codes) or to each family of agents (ATC4 codes) will be compared.

To avoid bias due to a lack of randomization, in both approaches, matching will be carried out between the groups with respect to confounding variables. In addition, if residual confounding is suspected or an imbalance between groups remains after matching, adjustments for age, sex, and diagnostic groups will be performed. A Cox regression model will be constructed to estimate the effect of the evaluated drug. The hazard ratio (HR) and its 95% CI will be reported. Hazard proportionality will be assessed graphically by Schoenfeld residuals.

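### The death-database exclusion in Data Curation contradicts the rule that patients with no recorded death count as alive; separately, the postdeath-record exclusion selects on outcome

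*Protocol article*

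**What the plan says.** The last paragraph of Data Curation sets out who is rejected when the databases are merged. One rule reads: "In addition, all patients without registration or enumeration in the death databases will be excluded". The next reads: "Finally, patients with inconsistent dates will be excluded, for example, with postdeath records in the CMBD, ECAP, or electronic prescription".

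The Statistical Analysis section handles patients without a death entry differently: "Patients who are censored, for whom no death is recorded during the follow-up time, are considered alive at the end of the period".

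On the source of death data, the Data Sources section states: "The registry of causes of death is prepared by the INE using data from the Medical Certificate of Death or Statistical Bulletin of Death". Outcome Variables and Measurements names that registry as the only source of the outcome date: "Date of death (data source: INE cause of death registry". Survival runs from entry "until death or until 5 years of follow-up are reached".

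**The concern.** The INE registry is compiled from certificates and bulletins of death, so a living person has no entry in it. A rule that rejects everyone without an entry rejects the living, whereas the Statistical Analysis section keeps them and counts them as survivors. Both instructions cannot be applied to the same patient.

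The conflict falls on the core of the study. The exposure odds ratio compares patients alive at 5 years with those who died, the association rules have 5-year survival as their consequent, and Table 2 counts survivors. Data Curation does not limit the rule to cohort 1, so the literal reading would also reach the cancer-free controls that are used to discard findings.

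The second rule raises a smaller issue. A record can be dated after death only in someone with a death date, so this example of inconsistent dates rejects deaths and never survivors. It also drops the whole patient rather than the record. If the chance of rejection among the dead depends on exposure to the drug under study, the exposure odds ratio is distorted.

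**Working it through.** **The plan's own sample-size figure.** For 20% against 30%, two-sided 5%, 80% power and pooled variance: n = [1.96·√(2·0.25·0.75) + 0.8416·√(0.2·0.8 + 0.3·0.7)]² / 0.1² = (1.2002 + 0.5119)² / 0.01, just over 293, rounded up to 294 per group. The stated 294 reproduces. It does not depend on the curation rules, so this point leaves it unchanged.

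**Rule 1: the two instructions side by side.**

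| Patient | Data Curation, read literally | Statistical Analysis |
|---|---|---|
| Died within 5 years, in the registry | kept | died |
| Alive at 5 years, died later and before extraction | kept | alive at 5 years |
| Alive at extraction, no registry entry | excluded | alive at 5 years |
| Died but not linked, no registry entry | excluded | would be counted as alive |

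The sections conflict in the last two rows. In a registry that holds only deaths, those two kinds of patient look the same, and the article names no other source that would tell them apart.

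**Rule 1: how many patients are at stake.**
- Inputs: Table 2 gives 18,148 new cases a year and 2,401 expected 5-year survivors (sums over its nine rows). Sample Size Considerations gives 102,860 patients in the database.
- Average 5-year survival: 2401 / 18148 = 13.2%. Applying it to the whole database assumes the same mix of cancers as in Table 2.
- Expected 5-year survivors: 102,860 × 0.1323 ≈ 13,600. At 5% survival the count is 5,143, and at the 20% ceiling it is 20,572.
- Let g be the share of 5-year survivors who died after year 5 and before extraction. The literal rule keeps 102,860 × 0.1323 × g of them, alongside about 89,250 deaths within 5 years (102,860 − 13,608).

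| g (assumed) | 5-year survivors kept | Apparent 5-year survival |
|---|---|---|
| 0 | 0 | 0% |
| 0.10 | 1,361 | 1.5% |
| 0.25 | 3,402 | 3.7% |
| 0.50 | 6,804 | 7.1% |

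No extraction date is given, so g is unknown. The table shows a range and does not estimate the loss.

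**Rule 2: effect on a null odds ratio.** Let a proportion e be exposed among both survivors and deaths (true odds ratio 1). Let r_exposed and r_unexposed be the shares of exposed and unexposed deaths rejected. After rejection, the exposure odds are e/(1 − e) in survivors and e(1 − r_exposed) / [(1 − e)(1 − r_unexposed)] in deaths. Their ratio is (1 − r_unexposed) / (1 − r_exposed).

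| Exposed / unexposed deaths rejected (assumed) | Odds ratio under no effect |
|---|---|
| 1% / 1% | 0.99/0.99 = 1.00 |
| 2% / 1% | 0.99/0.98 = 1.01 |
| 5% / 1% | 0.99/0.95 = 1.04 |
| 10% / 1% | 0.99/0.90 = 1.10 |
| 1% / 5% | 0.95/0.99 = 0.96 |

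The last row shows that the direction is not fixed either. Whether such a shift would reach P<.05 depends on the size of the analysis. With 13.2% survival and 20% exposed in an unmatched comparison, a true null is rejected 7% of the time at 2%/1% and 43% at 5%/1% with all 102,860 patients. With 5,000 patients the figures are 5% and 7%.

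**The case against.** **On rule 1**, the defence is that the wording is loose and nothing more. The sentence sits in a paragraph about consistency between databases, and its reference to enumeration can mean that the patient could not be identified or linked for vital status. Every planned survivor analysis needs living patients. The Results section says that curation is done and analyses have begun, and a rule that removed the living would have been noticed. This stands as an account of intent. It does not remove the conflict, because the text does not say linkage and does not say how a linked living patient is recognised.

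**On rule 2**, there are four fair replies.
- Postdeath records are only an example. The wider rule on inconsistent dates can also remove survivors. This is correct.
- A postdeath record may signal a wrong death date or a wrong link, so rejecting the patient is defensible. This is also correct, and is a reason to ask for a sensitivity analysis instead of replacing the rule.
- Findings reproduced in the controls will be discarded, which should catch some artefacts. This helps only in part: controls die at different rates, so the same artefact need not show up there.
- Drugs prescribed in the 3 months before death are already set aside. This loosens the link between late records and counted exposure without removing it. It also means that a postdeath prescription carries no exposure information, so deleting the record alone loses nothing.

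**Stronger readings that the documents do not support.**
- A reader might infer that the long-survivor group has in fact been deleted. The planned analyses point the other way, and even the literal rule keeps survivors who died after year 5.
- A reader might infer that the inclusion criterion "who have complete data regarding the study variables" also shuts out the living, because date and cause of death are study variables. Date of surgery is on the list for cohort 1 too, and nobody would take that to exclude unoperated patients.
- A reader might infer that rule 2 mainly removes patients with dispensing and so makes drugs look protective. The rule names three sources and gives no frequencies. Patients without prescription records are already rejected, so those not exposed to a given drug also have records that can trigger rejection.
- A formula of 1/(1 − q), with q the share of exposed deaths rejected, gives 1.05, 1.11 and 1.25 at 5%, 10% and 20%. It needs near-zero rejection of unexposed deaths, which nothing in the article supports.

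**Conclusion.** The death-database rule and the handling of patients with no recorded death contradict each other and must be reconciled. As stated, the rule gives a wrong result for the primary alive-versus-dead comparison. About 13,600 expected 5-year survivors are at stake if Table 2's average applies to the database. The number that the literal rule would lose cannot be derived, and a drafting fault is more likely than a real intent to drop survivors.

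The postdeath-record rule selects on outcome in the example given. It biases the odds ratio only if rejection differs by exposure. Neither its size nor its direction follows from the documents, and it may be negligible. It is a secondary point.

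**What to change.** **Rule 1.** Replace the sentence in Data Curation with: *Patients whose identifier could not be linked for vital status are excluded; linked patients with no death record within 5 years are considered alive.* State how linkage is established, since a registry of deaths cannot by itself distinguish a living patient from an unlinked one. Because the Results section says that curation is complete, confirm which version of the rule was applied and rerun that step if it was the literal one.

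**Rule 2.** Keep the rule if preferred. Report the number rejected by rule, vital status and exposure, and add a sensitivity analysis that keeps these patients and deletes only the records dated after death.

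**Cost.** One sentence, one table and one further run of the analyses. The downside is that the sensitivity analysis keeps a few patients whose death date or linkage is wrong.
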